# RESPONDER – diagnosis of pathological complete response by vacuum-assisted biopsy after neoadjuvant chemotherapy in breast Cancer - a multicenter, confirmative, one-armed, intra-individually-controlled, open, diagnostic trial

**DOI:** 10.1186/s12885-018-4760-4

**Published:** 2018-08-25

**Keywords:** Breast cancer, Neoadjuvant chemotherapy, Treatment response evaluation, Vacuum-assisted biopsy

## Abstract

**Background:**

Neoadjuvant chemotherapy (NACT) is a standard approach of the multidisciplinary treatment of breast cancer. Depending on the biological subtype a pathological complete response in the breast (bpCR) can be achieved in up to 60% of the patients. However, only limited accuracy can be reached when using imaging for prediction of bpCR prior to surgery. Due to this diagnostic uncertainty, surgery after NACT is considered to be obligatory for all patients in order to either completely remove residual disease or to diagnose a bpCR histologically. The purpose of this trial is to evaluate the accuracy of a vacuum-assisted biopsy (VAB) to diagnose a bpCR after NACT prior to surgery.

**Methods:**

This study is a multicenter, confirmative, one-armed, intra-individually-controlled, open, diagnostic trial. The study will take place at 21 trial sites in Germany. Six hundred female patients with breast cancer after completed NACT showing at least a partial response to NACT treatment will be enrolled. A vacuum-assisted biopsy (VAB) guided either by ultrasound or mammography will be performed followed by histopathological evaluation of the VAB specimen before standard, guideline-adherent breast surgery. The study is designed to prove that the false negative rate of the VAB is below 10%.

**Discussion:**

As a bpCR is becoming a more frequent result after NACT, the question arises whether breast surgery is therapeutically necessary in such cases. To study this subject further, it will be crucial to develop a reliable test to diagnose a bpCR without surgery.

During the study we anticipate possible problems in patient recruitment as the VAB intervention does not provide participating patients with any personal benefit. Hence, a proficient informed consent discussion with the patient and a detailed explanation of the study aim will be crucial for patient recruitment. Another critical issue is the histopathological VAB evaluation of a non-tumorous specimen as this may have been taken either from the former tumor region (bpCR) or outside of the (former) tumor region (non-representative VAB, sampling error).

**Trial registration:**

The trial has been registered at clinicaltrials.gov with the identifier NCT02948764 on October 28, 2016 and at the German Clinical Trials Register (DRKS00011761) on February 20, 2017. The date of enrolment of the first participant to the trial was on March 8, 2017.

## Background

Neoadjuvant chemotherapy (NACT) is a standard part of the multidisciplinary treatment of breast cancer [1]. Nowadays up to 30% of all breast cancer patients receive NACT [2]. NACT has been shown to be equivalent to adjuvant chemotherapy in terms of disease free, distant disease-free, and overall survival in several clinical trials and enables more breast cancer patients to receive breast-conserving therapy [3–6]. Depending on the biological subtype of the tumor, up to 60% of the patients achieve a pathological complete response in the breast (bpCR) [7, 8]. The most conservative definition of a bpCR was found to be a complete disappearance of invasive and in situ residual tumor disease in the breast (ypT0) [9–11].

Achieving a bpCR is a predictor for an improved disease free and overall survival, and it is used as a surrogate clinical endpoint for long term outcome [1, 4, 6, 10–16]. Only mediocre diagnostic accuracy can be reached when predicting a bpCR before surgery by a combination of multiple aspects such as tumor biology, the applied NACT regimen, and breast imaging results [8, 17–20].

Due to this diagnostic uncertainty, surgery after NACT is considered to be obligatory for all patients in order to either completely remove residual disease in non-bpCR cases or to diagnose a bpCR [21]. So far, surgery is the only valid diagnostic instrument to diagnose a bpCR. However, there is evidence that in cases of a shrinking tumor a less radical breast surgery is oncologically safe. [22]. The case of a clinical or imaging complete response (cCR), however, requires the diagnostic resection of (parts of) the initial tumor bed in order to confirm (or not) a possible bpCR histologically [6, 23].

## Methods/design

### Aims

The main purpose of this trial is to evaluate the accuracy of a vacuum-assisted biopsy (VAB) for a reliable diagnosis of a bpCR after NACT. The study is designed to prove the false negative rate of the VAB is below 10% (= sensitivity is 90% or above).

### Design

This study is designed as a multicenter, confirmative, one-armed, intra-individually-controlled, open, diagnostic trial. Patients will be recruited in 21 centers in Germany.

### Participants

Participants are female patients aged 18 years and older with primary breast cancer after NACT treatment which has been performed for at least 12 weeks and resulted in cPR or cCR (see below). Patients can be enrolled if the following inclusion criteria are met: any cT and cN stage, except cT4 stages; patient is scheduled to undergo any routine breast cancer surgical intervention planned according to guidelines (breast conservation or mastectomy); the residual intramammary target lesion or clip marker is visible in mammography and / or ultrasound; diagnosis of imaging complete or partial response according to RECIST 1.1 by mammography or ultrasound, according to local routine; in case of multicentric disease: confirmation of the same tumorbiological subtype of tumor defined by immunohistology in at least 2 lesions. Only one breast per patient will be included, in bilateral cancer one breast can be included. Patients have to be able to understand the character and individual consequences of the clinical trial and must give written informed consent before enrollment in the trial. Patients will be excluded from the trial in case of palliative or recurrent breast cancer. Further exclusion criteria are dislocation of clip marker (> 5 mm distance to the initial target lesion border at the time of clip placement), contraindication for VAB or associated procedures (e.g. local anesthesia) as well as pregnancy and lactation.

### Intervention

In this study design the control (breast surgery = reference test) and the comparator (VAB = index test) will both be performed on every patient. After an initial screening visit (visit 1), during which inclusion criteria will be checked and informed consent will be obtained, the VAB will be performed (visit 2). This intervention visit may vary by patient, tumor, and trial site characteristics and may either be an ultrasound guided or a stereotactically guided VAB. In analogy to the German S3 guideline on primary breast cancer management, we recommend to take at least 12 biopsies with 10G needles or less in case of larger needle sizes [24], bearing in mind that the probability of a sampling error might be reduced by taking more samples. As quantification of the specimen is not easily possible during the VAB (weight, as well as the number of biopsies taken does not necessarily quantify the amount of adequate tissue), we propose to take as many samples as reasonably justifiable (according to the local investigator). The VAB will be performed according to standards in primary breast diagnostics and according to the above mentioned guidelines. The intervention may be performed before surgery at a separate visit, the day before surgery (e. g. during the wire location), or in the operation room immediately prior to surgery depending on the site specific organizational setting. As the surgery will be performed according to clinical routine, there is no specific time frame for each trial visit. The physician performing the biopsy will be asked to quantify subjectively the level of representativeness of the biopsy (secondary outcome measure). The imaging performed during VAB may not be used for assessment of inclusion/exclusion criteria. Specimen radiography may be applied as an optional procedure after VAB to assess the representativeness of the specimen radiologically (secondary outcome measure). Standard surgery is regarded as the third trial visit (visit 3) as standard surgical excision (either breast conserving surgery or mastectomy) is the reference test. Adverse events will be documented until the end of visit 3.

### Adverse events

Possible adverse events of the VAB procedure may occur while the biopsy is taken. Due to the simple study design following clinical routine, very few adverse events are expected. Within the pilot study [25] there were no safety issues. As the biopsy is an additional minimal invasive intervention, it is accompanied by a number of possible risks. Those include bleeding with (1) hematoma and (2) possible urgent surgical intervention, infection, and injuries of surrounding tissue. Theoretically, VAB could challenge the surgeon, e. g. due to a hematoma and may lead to limitations in reliably assessing (3) the final tumor size or (4) the resection margins by pathology. The first two are informative but not critical; the latter situations are also possible even without preoperative VAB but should not exceed 10% of the patients (ypTx </= 10% and final R1 / Rx status </= 10%). We propose to interrupt the study as soon as those cases exceed 10% of the whole cohort.

### Intervention assignment and blinding

There will be no randomization within this one-armed study design.

To be able to transfer the results to future management concepts (e. g. omitting surgery in cases of VAB – proven bpCR) the histopathological, study specific evaluation of the VAB specimen will be performed independently of the routine diagnostic evaluation. Nevertheless, the local pathologist will have access to information on pre-NACT histopathological result, cT stage, ycT stage, estrogen receptor status, progesterone receptor status, Her2neu status, grading, and ki-67 status (if available). However, she / he will not receive any information regarding post-NACT surgical specimen results. All pre-surgical variables should be available and included in the pathological evaluation of the VAB specimen after NACT. The interdisciplinary team, including the breast surgeon as well as the patient, will also be blinded to pathological results of the VAB specimen until the final pathological report of the surgical specimen. This will ensure an unbiased surgical intervention.

Pathological work-up of VAB specimens will be performed in analogy to the primary diagnostic setting of suspicious breast lesions [26]. In order to achieve consistency among pathologists regarding the criteria for evaluation of the VAB specimen, a standard operating procedure will be provided as well as a the possibility of using a reference pathologist’s second opinion.

The pathological results of the VAB specimen will be categorized as follows:

**Table Taba:** 

Category A	Residual tumor cells in VAB specimen (= non-bpCR)
Category B	No residual tumor cells in the VAB specimen and VAB representative of former tumor region (= bpCR in VAB)
Category C	No residual tumor cells in the VAB specimen but VAB unclear representative or not representative of former tumor region (= possible sampling error)

Category C VABs are categorized as uninformative for the primary endpoint of the clinical trial.

The investigators assume that there is no difficulty to diagnose a “Category A” VAB result. The challenging topic is defining a VAB specimen to be pathologically representative of the former tumor region (tumor bed) or not, i. e. to differentiate between “Category B” and “Category C”. Only representative VAB samples are informative.

To evaluate intra- and interrater reliability of pathological evaluation of VAB specimen all local pathologists will be asked to send pre-NACT biopsy specimen and post-NACT VAB specimen (H&E sections or virtual microscopy files) of all non-tumorous VABs to the Department of Pathology Heidelberg (“pathological sub-study”). Slides will be digitized, pseudonymized, and returned to different local pathologists. Intra- and interrater reliability evaluation will be performed by at least five pathologists participating in the trial.

### Outcomes and measurements

The primary outcome is the false negative VAB result, i.e. the non-detected residual tumor by VAB compared to breast surgery. We will report this outcome as the false negative rate (FNR = rate of patients with non-detected residual tumor by VAB compared to breast surgery) which is a commonly used and validated measure in diagnostic studies. The FNR will serve as outcome measure in the cohort of the confirmatory primary outcome analysis. It will be calculated as the quotient of the number of cases with bpCR in VAB (“Category B”) and residual tumor in surgical specimen (false negative VAB results), divided by the total number of cases with residual tumor in either specimen (VAB and / or surgical specimen). Residual tumor is defined as a positive result, in surgical specimen as well as in VAB.

As our secondary outcomes we will use true negative and true positive results compared to breast surgery. The standard definitions are applied.

### Statistical procedures

#### Sample size calculation

As the primary endpoint we use the rate of patients with non-detected residual tumor (=false negative cases), the sample size calculation refers to the required number of patients for which surgery revealed a residual tumor. This number depends on the prevalence of residual tumor in the whole cohort. Motivated by previous works and the definition of the inclusion and exclusion criteria, we assume that this prevalence is at least 0.5. For the test hypotheses the sample size required to achieve a power of 0.8 is given by 238 cases (calculated with the software ADDPLAN Version 6.1.1). Consequently, a total of 476 patients have to be recruited to reach the required number of cases with residual tumor. As the prevalence of 0.5 is only an estimator and, moreover, some patients may be excluded from the analysis because of an unclearly representative VAB, we add an exclusion rate of 0.25 according to the findings in the pilot study [25]. This results in a total number of 595 patients, which will be rounded up to 600 patients, to be assigned to the trial.

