### Analysis strategy

#### Primary efficacy analysis

The null hypothesis to be assessed within the confirmatory analysis states that the rate of patients with non-detected residual tumor p is larger or equal to 0.1. Whereas the alternative hypothesis, for which this trial is powered, states that p is at most 0.05. The test hypotheses are thus given by.

H0: *p* ≥ 0.1 versus H1: *p* < 0.05,

which are tested with the one-sample Binomial-test at a one-sided significance level of α = 0.025.

The rate of patients with non-detected residual tumor p is estimated by the number of cases with diagnosed bpCR in VAB divided by the number of all patients for which surgery or VAB revealed a residual tumor.

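### The 25% exclusion allowance multiplies by 1.25 instead of dividing by 0.75, so on the plan's own inputs 600 patients yield about 225 residual-tumour cases rather than 238, and power is about 76-77%

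*Protocol article*

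**What the plan says.** All of the sizing is in the protocol article under Sample size calculation; the test is under Primary efficacy analysis.

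- **Hypotheses.** Under the null, "the rate of patients with non-detected residual tumor p is larger or equal to 0.1". The alternative, "for which this trial is powered, states that p is at most 0.05".
- **Test.** A "one-sample Binomial-test at a one-sided significance level of α = 0.025".
- **Cases needed.** "the sample size required to achieve a power of 0.8 is given by 238 cases".
- **Prevalence of residual tumour.** "we assume that this prevalence is at least 0.5". The planning value is 0.5, which gives 476 patients. The same paragraph concedes that this value is only an estimate.
- **Exclusions.** Because "some patients may be excluded from the analysis because of an unclearly representative VAB, we add an exclusion rate of 0.25", a rate taken from the pilot study.
- **Total.** "This results in a total number of 595 patients, which will be rounded up to 600 patients".

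Under Primary analysis set, the confirmatory cohort is everyone recruited minus Category C patients, whose biopsy is tumour-free but not clearly representative.

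**The concern.** The primary analysis set is formed by removing patients from those recruited, so an exclusion rate is a share of recruited patients. To be left with 476 after losing a quarter, one divides 476 by 0.75. The plan adds a quarter of 476 instead. Its stated total therefore does not return the number of cases it calls required, on the prevalence and exclusion rate it states itself.

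At stake is the power claimed for the trial's only confirmatory test. The allowance is also meant to absorb error in the prevalence estimate. Applied this way it does not fully cover the exclusions, so nothing is left over for prevalence.

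A second, separate question is whether 238 cases give 80% power for the test named. The formula that reproduces 238 is a normal approximation, whereas the test is described as binomial.

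**Working it through.** **Inputs, all from the protocol article.** p0 = 0.10, p1 = 0.05, one-sided α = 0.025 (Primary efficacy analysis); power 0.8, 238 cases, prevalence 0.5, exclusion rate 0.25, total 595 rounded to 600 (Sample size calculation).

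**1. Reproduce 238.** One-sample normal approximation:

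n = [(z₀.₉₇₅·√(p0(1−p0)) + z₀.₈₀·√(p1(1−p1))) / (p0−p1)]²
= [(1.960 × 0.3000 + 0.8416 × 0.2179) / 0.05]² = 238.03.

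This matches the stated 238. Other common formulas do not: arcsine gives 211.9 and the continuity-corrected version 257.6.

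**2. Reproduce 476 and 595.** 238 / 0.5 = 476. 476 × 1.25 = 595, exactly the stated figure.

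**3. Apply the exclusion as a share of those recruited.** 476 / (1 − 0.25) = 634.7, so 635. Check: 635 × 0.75 × 0.5 = 238.

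**4. Cases that 600 delivers.** If Category C is unrelated to residual-tumour status, 600 × 0.75 × 0.5 = 225, which is 13 short of 238. (595 gives 223.)

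**5. Power at a false negative rate of 5%.** The normal approximation is Φ{[(p0−p1)√n − 1.960·√(p0(1−p0))] / √(p1(1−p1))}. The exact test rejects at the largest count c for which P(X ≤ c | n, 0.10) ≤ 0.025, and its power is P(X ≤ c | n, 0.05).

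| Cases | Normal approximation | Exact cut-off | Exact α | Exact power |
|---|---|---|---|---|
| 225 | 77.1% | ≤13 | 0.0173 | 76.2% |
| 238 | 80.0% | ≤14 | 0.0170 | 78.6% |
| 240 | 80.4% | ≤14 | 0.0154 | 77.7% |
| 255 | 83.3% | ≤16 | 0.0247 | 85.9% |
| 270 | 85.8% | ≤17 | 0.0218 | 86.7% |
| 300 | 89.9% | ≤19 | 0.0171 | 88.1% |

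With the case count treated as random, Bin(600, 0.375), average exact power is 76.7%.

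**6. Loss due to the slip, like for like.** Approximate: 80.0 − 77.1 = 2.9 points. Exact: 78.6 − 76.2 = 2.4 points.

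**7. Exact power is saw-toothed.** It is at least 80% at 231-234 and at 243-252, below 80% at 235-242, 253 and 254, and at least 80% for every n from 255 on. The 78.6% at 238 is partly an effect of where 238 falls on the saw-tooth.

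**8. When 600 does yield 238 cases.**
- Exclusions at prevalence 0.5: 1 − 476/600 = 20.7% at most.
- Prevalence at 25% exclusion: 238 / (600 × 0.75) = 0.529 at least.
- Uneven exclusion: 600 × 0.5 = 300 residual-tumour patients are recruited. Losing 15%, 10% or none of them leaves 255, 270 or 300 cases (exact power 85.9%, 86.7%, 88.1%).

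**9. If prevalence is lower.** At 25% exclusion, average exact power is about 71% at prevalence 0.45 and about 65% at 0.40.

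**The case against.** The strongest objection is that 225 rests on an assumption the plan does not state. Category C requires a biopsy without tumour cells, so a residual-tumour patient can be excluded only if the biopsy missed the tumour. Losing a quarter of residual-tumour patients while the false negative rate among the rest is 5% would mean that the biopsy found tumour in only 0.75 × 0.95 = 71% of them. If exclusions fall mainly on patients with complete response, the shortfall shrinks or disappears. This stands as a condition on the result. It does not rescue the published arithmetic, which applies 0.25 to all patients and gives no split. Category C is also labelled a possible sampling error, so residual-tumour patients can fall into it.

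Second, prevalence is given as a floor, and about 0.53 would be enough. That also stands, but the calculation uses 0.5 and the same paragraph treats that value as uncertain.

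Third, the plan does not say that the binomial test is exact. That is fair. The exact figures hold only if it is, and for that reason the inflation slip is also measured on the approximation's own scale.

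A reader might go further and infer that the slip alone takes power from 80% to 76%, that 600 patients cannot reach 238 cases, or that recruitment must rise to 635. The documents support none of these. The first compares an exact figure with an approximate one. The second ignores the conditions in step 8. The third does not follow from a loss of 2 to 3 points, and 635 would only restore 238 cases, with exact power of 78.6% (79.5% averaged over a random case count).

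**Conclusion.** The error is confirmed: 595 comes from 476 × 1.25, where a 25% exclusion of recruited patients needs 635. With prevalence 0.5, and exclusion unrelated to residual-tumour status, 600 patients give about 225 evaluable cases. Power is then about 76-77%, and the stated 80% does not follow from the stated inputs.

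The exact-test point is separate and smaller. If the binomial test is run exactly, 238 cases already fall slightly short of 80%, whatever happens with exclusions.

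Severity is moderate. The analysis set and the decision rule are untouched, and type I error stays controlled. The true split of Category C could make actual power higher than stated here; a prevalence below 0.5 would make it lower.

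**What to change.** Keep 600 and correct the sample size paragraph:

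1. State that, with 25% exclusion and prevalence 0.5, 600 patients are expected to give about 225 residual-tumour cases and power of about 76-77% at a false negative rate of 5%. Give 635 as the total that would correspond to a true 25% exclusion.
2. State that 600 yields the planned 238 cases only if exclusions are at most about 20.7%, or prevalence is at least about 0.53, or Category C falls mainly on patients with complete response. If the sponsor relies on the last of these, the assumed split should be written down.
3. Say whether the binomial test is exact, and quote power for that version. For the exact test, give the cut-off with the case count (≤13 of 225, ≤14 of 238) and note that power stays at or above 80% for every n only from 255 cases.
4. Do not write that 20% exclusions give 80% power without saying that this is the normal approximation: 600 × 0.80 × 0.5 = 240 cases has exact power of 77.7%.

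The cost is a reworded paragraph and a slightly less favourable stated power. No extra patients are needed.

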### Analysis variables

#### Derivation of the primary endpoint

The false negative rate (FNR) will be calculated as the quotient of the number of cases with “pCR in VAB” and residual tumor in surgical specimen (false negative VAB results), divided by the total number of cases with residual tumor in surgical specimen and / or VAB in the cohort of the confirmatory primary outcome analysis (= primary analysis set).

#### Derivation of secondary endpoints

Specificity, negative, and positive predictive values will be calculated according to the standard definitions.

